**Outcome 2C):** Mean increase in maximum resting pressure by at least 50%.

**Objective 3) LUT, bowel and sexual functions (long-term TCSCS):** To test whether targeted long-term TCSCS (6-week trial) is safe and can improve urinary and faecal continence in humans with chronic SCI.

**Objective 3A)** To test whether targeted long-term TCSCS can improve urinary and faecal continence.

**Hypothesis 3A)** Long-term TCSCS will improve urinary and faecal continence. These improvements will be greater in individuals who complete intensive long term TCSCS compared to individuals who complete moderate long term TCSCS.

**Outcome 3A):** Mean decrease in the frequency of urinary and faecal incontinence by at least 50%.

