**Objective 3C) To assess persisting effects of long-term TCSCS on LUT, bowel and sexual function.**

**Hypothesis 3C):** The longevity of the beneficial effects on LUT, bowel and sexual function, after cessation of TCSCS, will be greater in the group that received intense stimulation versus the group that received moderate stimulation.

**Outcome 3C):** Maintained improvements in urinary and faecal incontinence (AIM 3A) and sexual function (AIM 3B) at 6 and 12 weeks after the cessation of TCSCS.

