### Statistical Plan

Statistical analysis on LUT, bowel and sexual function will be performed (n = 40 with SCI).

A sample size calculation was performed using G\*power, version 3.0.10, with power set at 0.8 and  $\alpha$  at 0.05. Data from participants that match our inclusion criteria (n = 5, level of lesion C5 – T10, motor-complete AIS, A or B) were used from a recent TCSCS study. A minimum sample of 26 participants is required to detect a significant change in voiding efficiency [voided volume / (voided volume + post-void residual volume)] with short-term TCSCS (stim-off =  $37.8 \pm 40.6\%$  vs. stim-on =  $58.2 \pm 39.4\%$ , effect size = 0.510). Presently, there are no long-term TCSCS data with LUT and bowel outcomes, consistent with those proposed in this protocol, to facilitate a meaningful power calculation. Therefore, given this is a pilot trial study, and in order to account for drop out with long-term TCSCS, we aim to investigate 40 individuals with SCI (n = 40, C5 – T6). Short-term TCSCS effects on UDS parameters (AIM 2A) as well as ARM testing (AIM 2C) with or without different stimulation configurations will be assessed using a repeated measures non-parametric analysis of variance (ANOVA), i.e. Kruskal–Wallis test. Data from the repeatability portion of the study (AIM 2A) will be assessed within (same session) and between (different sessions) visits (2 and 3) using a repeated measures non-parametric ANOVA. TNFBM will also be assessed using a repeated measures non-parametric ANOVA.

Long-term TCSCS: Differences in continuous variables for questionnaire data (NBSS, NBD Score, I-QoL, IIEF-15 or FSFI) in AIM 3 will be assessed using a two-way repeated measures [baseline, immediately post long term TCSCS as well as post-interventional follow up at 6 and 12 weeks] ANOVA comparing changes between moderate and intensive TCSCS. Furthermore, UDS testing as well as 'faecal continence severity' (baseline and end of TCSCS 6-week period) will be assessed using Wilcoxon signed-rank tests within

groups. A P-value less than 0.05 will be considered statistically significant. A complete thematic analysis will be performed to collect contextual qualitative data from the sexual health interview.

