#### *Bowel assessment*

- Neurogenic bowel dysfunction score (NBD Score)
- The modified Wexner fecal incontinence score (WIS)
- Time Needed for Bowel Movement (TNFBM), completed at home

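### The dedicated faecal continence measure is tested only within each dose group and only to the end of treatment, so it cannot answer the between-dose and persistence claims of Hypotheses 3A and 3C

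*Protocol*

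**What the plan says.** **Hypotheses.** Under Objectives, Hypotheses and Outcomes, Hypothesis 3A covers urinary and faecal continence and adds: "These improvements will be greater in individuals who complete intensive long term TCSCS compared to individuals who complete moderate long term TCSCS". Hypothesis 3C says that the benefit on LUT, bowel and sexual function will last longer in the intensive group. Outcome 3C judges this by "Maintained improvements in urinary and faecal incontinence (AIM 3A) and sexual function (AIM 3B) at 6 and 12 weeks after the cessation of TCSCS". Outcome 3A is "Mean decrease in the frequency of urinary and faecal incontinence by at least 50" per cent.

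**Tests.** In the long-term part of the Statistical Plan, a two-way repeated-measures "ANOVA comparing changes between moderate and intensive TCSCS" is assigned to "questionnaire data (NBSS, NBD Score, I-QoL, IIEF-15 or FSFI) in AIM 3". Its time points are baseline, immediately after treatment, and 6 and 12 weeks later. The next sentence turns to "UDS testing as well as 'faecal continence severity"' and says of these: "baseline and end of TCSCS 6-week period) will be assessed using Wilcoxon signed-rank tests within" groups.

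**Data.** The bowel assessments at baseline, after treatment and at both follow-ups (weeks 19 and 25) include "The modified Wexner fecal incontinence score (WIS"). Urodynamics (UDS) is last done at the single post-treatment visit in week 13; the two later visits are by telephone.

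**The concern.** The protocol fixes a test that does not match its hypothesis. A within-group signed-rank test asks whether a group changed from baseline. Hypothesis 3A asks whether one group changed more than the other, and Hypothesis 3C asks whether that advantage persists after stimulation stops. For faecal continence severity the stated analysis does neither. This is not a detail left open for a later analysis plan, because the protocol names the test, the time points and the comparison.

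The risk lies in how the result will be read. If the intensive group reaches p < 0.05 and the moderate group does not, the natural conclusion is that intensive treatment works better for faecal continence, as the hypothesis predicts. That pattern arises often when the two doses work equally well. Faecal incontinence is one of the two components of Outcome 3A. The long-term phase has no unstimulated arm, so the dose contrast is the only concurrent comparison it offers.

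**Working it through.** **1. Hypotheses against tests**

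| Measure | Between-dose test | Tested at 6 and 12 weeks after treatment | Collected then |
|---|---|---|---|
| NBSS (its incontinence domain is named primary for Aim 3A) | yes | yes | yes |
| NBD Score (constipation and faecal incontinence combined) | yes | yes | yes |
| I-QoL, IIEF-15 or FSFI | yes | yes | yes |
| Faecal continence severity (taken as Wexner) | **no** | **no** | **yes** (Wexner) |
| UDS | **no** | no | no |

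The faecal continence row lacks what Hypotheses 3A and 3C need, although the data will exist.

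**2. The protocol's own sample-size figure**

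The minimum of 26 is for a within-person, short-term change in voiding efficiency with effect size 0.510. A one-sided paired t-test at alpha 0.05 gives N = 26 (power 0.812), so it reproduces on that reading; a two-sided test needs 33. The figure does not bear on the dose comparison, for which the protocol says no meaningful power calculation was possible.

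**3. How often two within-group tests disagree when the doses are equally effective**

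Inputs: two-sided alpha 0.05 (0.05 is stated, sidedness is not); 20 per group (assumed, since only the total of 40 is given); the same true standardised change d in both groups (assumed, 0.3 to 0.7). Let p be the power of each within-group test, from the noncentral t with n − 1 degrees of freedom and noncentrality d√n. The chance that exactly one group is significant is 2p(1 − p).

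- d = 0.3: p = 0.247; 2 × 0.247 × 0.753 = 0.37
- d = 0.5: p = 0.564; 2 × 0.564 × 0.436 = 0.49
- d = 0.7: p = 0.844; 2 × 0.844 × 0.156 = 0.26

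The maximum is 0.50, reached when p = 0.5. By symmetry, half of these trials show intensive alone significant: about 19%, 25% and 13%.

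A simulation with the Wilcoxon signed-rank test itself gives 34% at d = 0.3, 48% at 0.51 and 17% at 0.8. In the same simulated trials a Mann-Whitney test on the changes rejects about 4% to 5% of the time, as it should when the doses do not differ.

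The result does not depend on 20 per group. With 17 per group, p is 0.214, 0.491 and 0.773 at d = 0.3, 0.5 and 0.7, giving 34%, 50% and 35%. With 13 per group, p is 0.169, 0.382 and 0.640, giving 28%, 47% and 46%.

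**4. What a direct comparison can deliver**

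For a two-sample comparison of change at two-sided alpha 0.05 and 80% power, the detectable difference is 0.91 SD at 20 per arm, 0.99 at 17 and 1.15 at 13. Power for a 0.51 SD difference at 20 per arm is 35%. The 95% CI half-width at 20 per arm is t(0.975, 38) × √(2/20) = 2.024 × 0.316 = 0.64 SD.

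**The case against.** **The NBD Score covers it.** The protocol describes this score as measuring faecal incontinence as well as constipation, and it is compared between doses out to 12 weeks. A reader might infer from the signed-rank sentence that faecal incontinence is never compared between doses; the documents do not support that. What remains is that the NBD Score also counts defaecation time, constipation, medication and skin problems, so a difference on it cannot be attributed to continence. It is an indirect test.

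**Urinary continence is handled correctly.** A reader might infer that Hypotheses 3A and 3C go untested as a whole. They do not: the NBSS, with the incontinence domain named primary for Aim 3A, gets the between-dose analysis at all four time points.

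**UDS is not a 3A or 3C outcome.** This stands. Neither outcome names it; it enters 3C only through the broad term LUT function. Its stopping at week 13 follows from the visit schedule rather than the choice of test. The missing between-dose comparison at week 13 is real but secondary.

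**The protocol does not say it will compare significance across groups.** True. The percentages above describe the reading that separate tests invite, not an announced rule.

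**Frequency is measured in part.** The NBD and Wexner scores contain frequency items, and the full Schedule of Events sits in an application section not shown. It would therefore be too strong to say that frequency goes unmeasured. It can be said that the visit lists shown schedule no incontinence diary after treatment, and that no stated analysis addresses a 50% fall.

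**It is a pilot.** This limits what a between-dose test can show. It argues for an estimate with an interval, not for leaving the comparison out.

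**Conclusion.** The concern holds for the dedicated faecal continence measure. Its stated analysis has no between-dose comparison and stops at the end of treatment, while the hypotheses claim a larger and longer-lasting benefit with intensive stimulation. Under equal true effects, separate within-group tests would split into one significant and one non-significant group in roughly a quarter to a half of trials (26% to 49% at the three effect sizes computed for 20 per group), against about 5% for a direct test.

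Three assumptions carry this. Faecal continence severity is taken to mean the Wexner score, which the protocol does not say; the undefined term itself needs correcting. The 20:20 split is not in the document. The standardised changes are illustrative. The mismatch between test and hypothesis depends on neither the split nor the effect sizes.

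The point does not extend to urinary continence, and it reaches UDS only as a secondary gap at week 13. Nor does it rest on any loss of participants from the repeated-measures ANOVA: the protocol states neither a drop-out rate nor a complete-case rule.

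**What to change.** 1. Define faecal continence severity as the Wexner score.
2. Add it to the between-dose longitudinal analysis in a model of its own, as for NBSS, NBD Score, I-QoL and IIEF-15 or FSFI, using weeks 13, 19 and 25. Preferably take baseline as a covariate and use all available visits.
3. Compare the change in UDS between groups at week 13, baseline-adjusted or rank-based, and state that persistence of UDS effects is not assessed.
4. Report the intensive-minus-moderate difference with a 95% CI. State that precision is limited (about 0.91 SD detectable at 80% power with an assumed 20 per arm), and label the within-group signed-rank tests descriptive.
5. Restate Outcome 3A in terms of scores that are collected: the NBSS incontinence domain and the Wexner score.

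The cost is protocol and analysis-plan wording. All the scores and the week-13 UDS are already scheduled, so no new visit or measurement is needed.

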## Participants

### Enrollment Goal

40 participants with SCI.

### Target Population

Adults 18-65 with >1-year post injury traumatic SCI at or above the T6 spinal segment with documented lower urinary tract dysfunction. (n = 40).

### Inclusion and Exclusion Criteria

#### *Inclusion:*

A participant with SCI must meet all of the following criteria in order to be eligible for inclusion:

1. Resident of British Columbia, Canada with active provincial medical services plan
2. Male or female, 18-65 years of age
3. Chronic traumatic SCI (non-progressive, with complete motor paralysis) at or above the T6 spinal segment.
4. >1-year post injury, at least 6 months from any spinal surgery.
5. Documented presence of bladder dysfunction
6. Documented presence of bowel or sexual dysfunction.
7. American Spinal Injury Association Impairment Scale (AIS) A, B.
8. Greater than or equal to antigravity strength in deltoids and biceps bilaterally
9. Hand function sufficient to perform Clean Intermittent Catheterization (CIC) or a committed caregiver to provide CIC for management of urinary bladder drainage.
10. Participants must have documented three days of bladder and bowel history prior to their baseline visit.
11. Willing and able to comply with all clinic visits and study-related procedures.
12. Able to understand and complete study-related questionnaires (must be able to understand and speak English or have access to an appropriate interpreter as judged by the investigator).
13. No painful musculoskeletal dysfunction, unhealed fracture, pressure sore, or active infection that may interfere with testing activities.
14. Medication dosage must be stable for period of 4 weeks prior to participation
15. Baclofen dose cannot exceed 60mg per day
16. Stable management of spinal cord related clinical issues (i.e., spasticity management).
17. Women of childbearing potential must not be intending to become pregnant, currently pregnant, or lactating. The following conditions apply:
  - a) Women of childbearing potential must have a confirmed negative pregnancy test prior to the baseline visit.
  - b) Women of childbearing potential must agree to use adequate contraception during the period of the trial. Effective contraception includes abstinence.

18. Must provide informed consent.

### Exclusion

A participant who meets any of the following criteria will be ineligible to participate in Study:

1. Presence of severe acute medical issue that in the investigator's judgement would adversely affect the participant's participation in the study. Examples include, but are not limited to clinically significant renal or hepatic disease; acute urinary tract infections; pressure sores; active heterotopic ossification; newly changed antidepressant medications [tricyclics]; or unstable diabetes. The following conditions apply:
  - a. Moderate and severe forms of renal dysfunctions (eGFR below 60 ml/min)
  - b. Clinically significant abnormal laboratory tests (ALT; Alkaline Phosphatase; Bilirubin [total]; GGT) as judged by the investigator.
2. Recent treatment with OnabotulinumtoxinA into the detrusor muscle (within 6 months of the baseline visit)
3. Persons requiring ventilator support
4. Clinically significant depression or ongoing drug abuse
5. Use of any medication or treatment that in the opinion of the investigator indicates that it is not in the best interest of the participant to participate in this study.
6. Intrathecal baclofen pump
7. Oral baclofen dose >60mg
8. Cardiovascular, respiratory, bladder, or renal disease unrelated to SCI or presence of hydronephrosis or presence of obstructive renal stones.
9. Any implanted metal in trunk or spinal cord under the sites of application of electrodes (between anode and cathode).
10. Any active implanted active implanted medical device, including, but not limited to neurostimulators, cochlear implants, pacemakers, implantable defibrillators, or drug delivery pumps.
11. Severe anemia (Hgb<8 g/dl) or hypovolemia
12. Participant is a member of the investigational team or his /her immediate family.
13. Participant has undergone electrode implantation surgery.
14. Participant with swollen, infected, and inflamed areas or open wounds on the area of stimulation

### Overview

Eligible participants with SCI (n = 40) who can commit to 6 visits, over 4-6 weeks, will complete for the short-term effects of TCSCS. Participants with SCI (n = 40) who can commit to the full 25-week timeline will complete and then progress to complete for the long-term effects of TCSCS. Eligible participants, enrolled into will attend 5 visits at ICORD , 1 visit at St. Paul's hospital. Eligible participants will attend 37 visits at ICORD, 1 visit at St. Paul's Hospital, and 2 visits by phone. With the exception of ARM (conducted at Gastroenterology Clinic, St. Paul's hospital, Vancouver), all experiments will be performed at the International Collaboration on Repair Discoveries (ICORD), Blusson Spinal Cord Centre (BSCC), UBC. TPlease see the Schedule of Events in section 9 of the application.

### Visit 0 Pre-Screening

Individuals who respond to study advertisements in BCSCI journal, ICORD website, or GF Strong bulletin board will be contacted by a clinical coordinator and will be pre-screened for eligibility (virtually or in

person) based on the study inclusion and exclusion criteria and the potential participant's self-report and/or medical records.

Based on this pre-screening, potential participants will be provided the study informed consent form via email, and will be given at least 24 hours to review the form and ask any potential questions and make their decision about potential participation in the study.

#### Visit 1 Screening – Weeks 1-2:

Approximately 1.5 hours

Individuals who agree to participate in the study will be invited for a screening assessment to confirm study eligibility. After the individual has provided informed consent, he/she will be assigned a unique study number and the information listed below will be collected. All eligible participants will undergo detailed neurological examinations in order to establish severity of SCI.

##### *Screening Assessments:*

- Inclusion/Exclusion Criteria confirmation
- Demographics
- Medical history and history of injury
- Concomitant medication use
- Weight and height
- Previous allergies and adverse events to medications
- Renal ultrasound will be included from annual evaluation of patients
- Pregnancy screening will be performed
- Depression screening - Patient Health Questionnaire-9 (PHQ-9) (please see Descriptions of Assessments for details)
- Autonomic dysfunction in Spinal Cord Injury (ADFSCI) questionnaire
- International Standards for Neurological Classification of Spinal Cord Injury (ISNCSCI) exam

#### Visit 2: Baseline Assessments – Weeks 3-4:

Approximately 1 hour.

All eligible participants will undergo baseline evaluation for severity of bladder, bowel, sexual and cardiovascular dysfunctions using the validated questionnaires listed below. Participants will also undergo baseline 24 hours ambulatory evaluation of cardiovascular functions. This test will be specifically scheduled on the day of bowel routine with detailed documentation of time of bowel routine and each of the bladder catheterisations.

##### *Low Urinary tract assessments*

- Neurogenic Bladder Symptom Score (NBSS)
- The Incontinence-QoL (I-QoL)

##### *Bowel assessments*

- Neurogenic bowel dysfunction score (NBD Score)
- The modified Wexner fecal incontinence score (WIS)
- Time Needed for Bowel Movement (TNFBM), at home

### *Sexual health assessments*

- The International Index of Erectile Function (IIEF-15) (male participants)
- The Female Sexual Function Index (FSFI) (female participants)
- Pregnancy test for female participants.

### *Cardiovascular assessments*

- 24 hrs BP monitoring (on day of bowel routine):
- 24 hrs diary of activities

### *Visit 3 /Baseline EMG Mapping of Spinal Cord Segments with TCSCS / Week 3-4*

Approximately 2 hours.

Participants will undergo baseline mapping using surface EMG (Delsys Inc., Natick, USA) and concentric needle EMG as per an established protocol to record muscle activation during transcutaneous spinal cord stimulation (mapping) (TESCoN, SpineX Inc., CA, USA) at different spinal cord levels and different intensity. Please see subsections entitled TCSCS, Surface EMG and Concentric Needle EMG in Descriptions of Assessments section for details.

### *Visits 4,5,6: Urodynamics and Anorectal Manometry – Weeks 4-6:*

Approximately 2.5 hours per visit.

Following Visits 1 (Screening) Visit 2 (baseline assessments) and Visit 3 (mapping visit) using a randomized counter-balanced approach, all individuals will be allocated into two distinct pathways:

- Pathway #1: individuals will start with Urodynamics, (UDS 1, Visit 4), followed by a second session of Urodynamics (UDS 2, Visit 5), and ARM (Visit 6).
- Pathway#2: individuals will start with ARM (Visit 4), followed by Urodynamics (UDS 1, Visit 5), and a second session of Urodynamics (UDS 2, Visit 6)).

TCSCS and Cardiovascular monitoring will be performed during UDS and ARM. Please see Description of Assessments for details of Urodynamics, ARM, TCSCS and Cardiovascular monitoring.

### *Visits 7 – 18 or 36: Long Term TCSCS – Weeks 7-12:*

Approximately 90 minutes per visit.

Participants will come to ICORD for long term TCSCS, either 2 days/week (moderate) or 5 days/week (intense) for 6 weeks for a total of either 12 sessions or 30 sessions. Please see Description of Assessments for the details of an individual session.

During the 6 weeks of long term TCSCS, TNFBM will be measured during participants' conventional bowel routines at home. Participants will be asked to record the time from 'suppository insertion' to 'when bowel evacuation is completed' once per week for the bowel movement completed mid-week during each week of the 6 week TCSCS pathway.

24 ABPM will be performed mid-way through the 6 weeks and during the final week of the 6 weeks of treatment in combination with the participants' bowel routine.

## Visit 19-20 OR 37 – 38: Immediate Post-TCSCS Assessments – Week : 13

Visit 19 or 37 (approximately 3 hours):

After the 6 weeks of TCSCS, all participants will complete 1 visit at ICORD including UDS assessments and a SCI severity assessment (ISNCSCI). Please see description of Assessments for details.

Visit 20 or 38 (approximately 1 hour):

A series of questionnaires on low urinary tract function, bowel function, cardiovascular function and sexual health will be conducted by telephone or video conference call (considering the present COVID-19 pandemic environment). The questionnaires are listed below and details can be found in the Description of Assessments Section.

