#### *Cardiovascular assessments*

- Autonomic dysfunctions in SCI (ADFSCI) questionnaire: Comprises of 21 questions, covering three domains, including general, medications, and autonomic dysreflexia symptoms and severity

## Visit 21-22 or 39 - 40 / Follow-Up Visits at 6 and 12 weeks after completion of stimulation protocol/Week 19 and Week 25

These visits will take place over the telephone to evaluate existing and new adverse events and concurrent treatments. During each of these follow-up phone Visits (39 and 40) at 6 and 12 weeks post completion of long term TCSCS, a series of questionnaires on low urinary tract function, bowel function, cardiovascular function and sexual health will be conducted by telephone or video conference call (considering the present COVID-19 pandemic environment). The questionnaires are listed below and details can be found in the Description of Assessments Section.

During visit 40, a sexual health clinician, with experience providing clinical care to individuals with SCI, will also conduct a semi-structured qualitative interview. Please see Description of Assessments for details.

Visit 21/39 will take approximately 1 hour and visit 22/40 will take approximately 1.5 hours.

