### *Semi-Structured Qualitative Interview*

Participants will be interviewed in person by a sexual medicine clinician at the Blusson Spinal Cord Injury Centre to ascertain qualitative information on sexual functioning. These interviews will be digitally recorded, transcribed verbatim and anonymized on completion. The interview schedule will include questions pertaining to the following: participants sexual history and current relationship status, level of

sexual drive, ability to orgasm, barriers to sexual activity, self-esteem, the use of ergogenic aids, and participants' perceptions of the role of TCSCS on sexual functioning. Female participants will be asked about lubrication quality, and male participants will be asked about erection quality (with and without pharmaceutical or prosthetic assistance), and their ability to ejaculate. Participants will be advised during the consent process that the clinician will be acting as a researcher during this interview and is therefore prohibited from providing clinical care or direct medical advice during the study. A complete thematic analysis will be performed using NVivo software (Version 9.0, QSR, Southport, UK). The expected duration of the interview will be approximately 30 – 45 minutes.

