#### Known Study Risks/Harms

- Through the period of study, any adverse event will be recorded using the adverse event report form in section 9 of the application. If an adverse event occurs during the testing session will be immediately stopped. In addition, the participant's primary care provider and UBC CREB will be notified as necessary if serious adverse events (SAEs) occur. In addition, the participant's primary care provider, UBC CREB, and the Data Monitoring Committee (DMC) will be notified as necessary if serious adverse events (SAEs) occur. A Data and Safety Monitoring Committee will comprise of 3 individuals external and independent to the study to review the adverse event reports and stop the study if the safety data are of sufficient concern. Any adverse effects will be reported to these individuals responsible for Data and Safety Monitoring Committee, as well as to the appropriate UBC ethics boards by the study coordinator.
- The urodynamics and ARM procedure will necessitate that the participant expose their genitals in the presence of the Principal Investigator or study health care professionals. Every effort will be made to ensure their comfort and privacy during the procedure as long as safety is assured. For the urodynamic assessment, once the catheter is implanted, the gown will be placed to cover their genitals. Due to the risk of high blood pressure, participants will not be left unattended during urodynamic assessments.
- Participants may experience stress as a result of answering questions related to symptoms of depression, bowel and bladder function, and sexual functioning/satisfaction. The depression, bowel and bladder function questionnaires used in this study are commonly used clinical screening tools. The sexual functioning/satisfaction questionnaires were carefully chosen as they have previously been used in individuals with SCI. These questionnaires will be delivered in a private setting, by a single sexual medicine clinician, with considerable experience delivering these assessment tools and discussing such sensitive topics with male patients with SCI. Participants will also be provided with the Fraser Health Crisis line in the informed consent document if they require immediate, free and confidential emotional support.
- Participants will be advised not to take Viagra, Clans or Levitra for 4 days before the urodynamic tests as this could cause a drop in blood pressure requiring medical attention.

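### The Objective 3 questionnaires appear to be taken on site at baseline and remotely after treatment, so mode of administration is mixed with change from baseline

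*Protocol*

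**What the plan says.** **Baseline.** Under Visit 2, "All eligible participants will undergo baseline evaluation for severity of bladder, bowel, sexual and cardiovascular dysfunctions using the validated questionnaires listed below". The list covers NBSS, I-QoL, NBD score, the modified Wexner score (WIS) and IIEF-15 or FSFI. No mode is stated in words.

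**Week 13.** For Visit 20 (moderate group) or 38 (intensive group), the questionnaires on urinary, bowel, "cardiovascular function and sexual health will be conducted by telephone or video conference call".

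**6 and 12 weeks.** Of Visits 21–22 or 39–40 the protocol says "These visits will take place over the telephone to evaluate existing and new adverse events and concurrent treatments", and it gives the questionnaires there by telephone or video as well.

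**Visit count.** In the Overview, participants in the short-term part "will attend 5 visits at ICORD" and one at St. Paul's Hospital. For the full schedule: "Eligible participants will attend 37 visits at ICORD, 1 visit at St. Paul's Hospital, and 2 visits by phone".

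**Interview and administrator.** The follow-up section places the sexual health interview at Visit 40, while the interview section says "Participants will be interviewed in person by a sexual medicine clinician at the Blusson Spinal Cord Injury Centre". On the sexual questionnaires, Known Study Risks/Harms says "These questionnaires will be delivered in a private setting, by a single sexual medicine clinician". No other section names an administrator for any questionnaire.

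**Analysis.** The Statistical Plan uses a two-way repeated-measures ANOVA on NBSS, NBD, I-QoL and IIEF-15/FSFI over baseline, post-treatment, 6 and 12 weeks, comparing moderate with intensive stimulation. It adds within-group Wilcoxon signed-rank tests for urodynamics and faecal continence severity.

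**The concern.** Outcome 3A is a mean fall of at least 50% in incontinence frequency, and the NBSS incontinence domain is labelled its primary outcome. Outcome 3B is a mean improvement in satisfaction with sexual life. Both are changes from baseline in self-reported, sensitive matters. Both groups receive stimulation, so within-person change is the trial's evidence that stimulation works at all.

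If every participant answers on site before treatment and over a call afterwards, a tendency to answer differently in the two settings is counted as treatment effect. Because everyone switches at the same point, no analysis can separate the two once the data are in.

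**Working it through.** **1. Is the baseline on site?** This is an inference.
- The six short-term visits are split as five at ICORD and one at St. Paul's, the latter for anorectal manometry. Visits 1, 2 and 3 and the two urodynamics visits make exactly five, so Visit 2 is one of them.
- Visit 2 includes 24-hour blood pressure monitoring. Its set-up needs a cuff to be fitted and three seated readings.
- Apart from manometry, "all experiments will be performed at the International Collaboration on Repair Discoveries (ICORD").
- Where remote contact is allowed (pre-screening, week 13, follow-up) the protocol says so. Under Visit 2 it does not.

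**2. Visit count, intensive schedule.**

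| Visits | ICORD | St. Paul's | Remote |
|---|---|---|---|
| 1–6 | 5 | 1 | 0 |
| 7–36 (stimulation) | 30 | 0 | 0 |
| 37 | 1 | 0 | 0 |
| 38, 39, 40 | 0 | 0 | 3 |
| Sum | 36 | 1 | 3 |

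The Overview states 37, 1 and 2. Both splits total 40. The Overview's split is reproduced only if Visit 38 is on site, which the Visit 38 text contradicts.

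**3. Mode by time point under each reading.**

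| Reading | Baseline | Week 13 | 6 weeks | 12 weeks |
|---|---|---|---|---|
| Visit descriptions | on site | remote | remote | remote |
| Overview count | on site | on site | remote | remote |

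Under the visit descriptions, mode coincides with before versus after treatment. Under the Overview count it changes between week 13 and 6 weeks, where it could imitate or hide a loss of effect in Outcome 3C. Neither reading keeps one mode throughout.

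**4. Which results are exposed (visit descriptions).** The 50% decrease in 3A, the mean improvement in 3B, the ANOVA time effect, any statement at 6 or 12 weeks relative to baseline, and the within-group Wilcoxon test if faecal continence severity means the WIS. Not exposed: contrasts among the three remote time points; urodynamics (on site before and after); time needed for bowel movement (recorded at home throughout); and the moderate-versus-intensive contrast, if the shift is the same in both groups and cancels.

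**5. Illustrative size.** The documents give no mode effect, so these inputs are assumptions: a pure mode shift of 0.1, 0.2 or 0.3 SD of the score towards improvement, no treatment effect, and a baseline-to-post correlation r of 0.6. A paired t test at two-sided 0.05 stands in for a before-after test.
- SD of change = √(2(1 − r)) = √0.8 = 0.894.
- SE of mean change = 0.894/√40 = 0.141 SD for 40 participants, and 0.894/√20 = 0.200 SD for one group of 20 (equal groups assumed).
- The chance of a significant improvement comes from the noncentral t distribution with noncentrality shift/SE; the nominal chance in that direction is 2.5%.

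| Shift (SD) | n = 20, r = 0.6 | n = 40, r = 0.6 | n = 40, r = 0.4 | n = 40, r = 0.8 |
|---|---|---|---|---|
| 0.1 | 7% | 10% | 8% | 16% |
| 0.2 | 16% | 28% | 20% | 50% |
| 0.3 | 30% | 54% | 39% | 83% |

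The n = 20 column is closest to the planned within-group test. The n = 40 columns describe a pooled before-after test that the plan does not state, and they allow for no dropout.

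**The case against.** The best defence is that the planned questionnaire analysis compares moderate with intensive stimulation, and that contrast is untouched by a common shift. This stands, and it limits the point to the before-after claims. Those claims are nonetheless how Outcomes 3A and 3B are worded.

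It can also be said that remote contact was chosen because of the pandemic, in a pilot study whose before-after contrast already carries expectation and time effects. That is fair. Harmonising mode will not make the contrast clean, but it removes one avoidable source of bias. The pandemic explains remote follow-up; it does not require a different mode at baseline.

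The on-site baseline is inferred partly from an Overview whose full-schedule count conflicts with other sections. This also stands. The monitor set-up supports the inference independently, and accepting the Overview's count moves the change of mode without removing it.

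Two stronger readings are tempting and are not supported:
- A reader might infer that the sections disagree on who gives the questionnaires. Only the risks section names anyone, and only for the sexual questionnaires. The others are silent, which is not disagreement.
- A reader might infer a second change of mode at 12 weeks from the in-person interview. That wording covers only the qualitative interview. The 12-week questionnaires are remote wherever their mode is stated.

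**Conclusion.** The point holds as a design weakness that is cheap to remove. By the visit descriptions, the Objective 3 questionnaires move from on site at baseline to telephone or video at all three later time points, so mode is mixed with change from baseline. This rests on the inference that Visit 2 is on site. By the Overview's count, the move comes after week 13 and touches persistence instead.

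The size and direction of any mode effect are unknown. A shift the other way would hide benefit. The percentages show what modest shifts could do under the stated assumptions; they do not estimate this trial's false-positive rate. The between-group comparison is not biased if both groups switch alike.

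Two contradictions are plain on the text: 37/1/2 against 36/1/3 visits, and Visit 40 by telephone against an interview in person. The second concerns the interview only.

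**What to change.** - Give each Objective 3 questionnaire in one mode at all four time points. One way is to take the baseline questionnaires by the same kind of remote call in weeks 3–4. Telephone and video are themselves two modes, so choose one for each participant and keep to it.
- State that the single clinician named in Known Study Risks/Harms gives the sexual questionnaires at every time point.
- Record the mode at each administration, and flag participants already enrolled with an on-site baseline.
- Reconcile the visit counts in the Overview with the sections on Visits 19–20 or 37–38 and 21–22 or 39–40, and the interview mode in the follow-up section with the interview section.

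The cost is protocol wording and one call in place of part of Visit 2, with no extra visit or staff. The downside is a mixed baseline mode across the trial if some participants are already enrolled, which the flag makes visible.
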